### Qualitative data collection

#### Qualitative interviews

An experienced qualitative researcher conducts in-depth individual interviews with a sub-sample of trial participants starting soon after the randomisation and finishing around 2–3 months after the 3-month follow-up period is complete. Interviews cover issues related to the interviewees’ experience of taking part in the trial; more specifically, their understanding of CHD risk, factors affecting their understanding, reaction to receiving information about risk and lifestyle advice, the extent to which understanding of risk contributes to motivation for behaviour change, the implementation of intention to change after receiving risk information and lifestyle advice, and the facilitators and barriers for such a change. The qualitative study focuses mainly on participants in the intervention arms because the lack of an intervention leaves little to discuss and explore qualitatively with the members of the control arm. However, in order to explore the impact of receiving different types of information in different stages, we aim to have up to six interviews with members of arms who initially received no intervention/only lifestyle advice/only phenotypic risk score, after they receive all their risk scores at the end of the intervention.

In order to supplement the quantitative data which is collected at only two time points (at baseline and 12 weeks later), we aim to interview different participants at different time points, interviewing some immediately after the randomisation, others half way through the intervention and others towards the end of the intervention or up to 3 months after it ends. Proportionally more participants whose risk score is medium or high are purposively recruited as this is the population most likely to have a stronger motivation to change their lifestyle. A subset of this group may be interviewed more than once – for example immediately after the start of intervention and then after the completion of the intervention in order to explore early expectations/motivation and compare them with later perceptions or behaviour. For the participants who do not express an intention to change their lifestyle and those who are approached at later stages of the intervention, the discussion on the reaction to receiving the risk scores or lifestyle advice is conducted retrospectively focusing on the period from receiving the risk scores and up to the point of the interview. Interviewees are asked to sign an interview consent form giving permission for their interview to be recorded.

#### Qualitative focus groups

Two to three focus groups are conducted at different points of time throughout the trial. Approximately 8–12 participants take part in each of the focus groups. These participants do not take part in the individual qualitative interviews. The focus groups are facilitated by an experienced qualitative researcher and one or two assistants from the research team. Participants are purposively selected in order to include people with various demographic backgrounds. However, at least two of the groups may be selected for gender homogeneity (male/female-only) in order to encourage greater participation in what may be considered a gender-sensitive issue. The focus groups cover issues related to the relationship between risk awareness, motivation for change and actual change of behaviour and lifestyle, but their main focus is on communication and understanding of CHD risk estimates as well as the lifestyle advice. We hope to benefit from the interactive aspect of the focus groups in order to gain as rich as possible feedback regarding the advantages and disadvantages of the forms of communication of risk and lifestyle advice used in the trial. Permission is sought from the participants, as outlined in the consent process, for the focus groups to be recorded and transcribed.

### Withdrawal

A participant is free to withdraw their consent from the study, at any time, without giving a reason. All requests from participants to withdraw from the study are directed to the study coordination team who will discuss the options for withdrawal. The study data manager places a flag on the research database to ensure appropriate use of data and notifies the study coordination team of withdrawal. University of Cambridge research staff instructs the central laboratory to remove all archive samples from the biorepository for participants who have been withdrawn from the study and who have requested no further use of their stored samples.

### Adverse events

This is a low-risk trial with little reason to consider that adverse events would arise as a result of following any of the interventions. Accordingly, no formal adverse event monitoring is planned. However, events may incidentally come to the attention of the research team (e.g. via interviews or focus groups, or direct communication with participants via the study coordination team) which will be recorded and followed up accordingly.

### Statistical analyses

#### Sample size calculation – randomised controlled trial

The primary outcome is between-group differences in the change (follow-up minus baseline) of the average acceleration (m/s^2^) over the observation period, measured using the Axivity AX3 3-Axis Logging Accelerometer®. The intervention will be potentially important if it increases the primary outcome by 10 %. This corresponds to an additional 10 min of brisk walking per day or an additional 3 min of jogging per day. The same effect size was used in the Understanding Risk trial by Price et al. [54] among people at high risk of CVD with one month of follow-up. This effect size is also in line with the ProActive trial that aimed to increase physical activity among individuals at high risk of type 2 diabetes [55]. To allow for four pairwise comparisons in the primary analysis, the significance level was set to 1.25 %. We calculated that 186 participants per group will be needed to detect this effect with 80 % power and 95 % confidence, assuming the estimated standard deviation (SD) of change in physical activity from baseline to follow-up is 0.05 and the correlation between physical activity at baseline and follow-up is 0.6 [56]. Allowing for an attrition rate of 20 %, we therefore aim to randomise a total of 932 participants (233 per group).

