#### Analysis design – randomised controlled trial

All trial analyses will be based on the Intention To Treat (ITT) principle. Those with missing follow-up data will be excluded from the analyses (a complete case approach). We will perform sensitivity analyses to assess the impact of missing follow-up data on the results. Participants with missing baseline data will be included in the analyses using the missing-indicator method [59].

The null hypothesis for the primary analysis is that there is no difference between any of Groups 1 to 4. Estimates of the following pairwise differences will be calculated: 1) Group 1 (control group) vs. Group 2 (lifestyle advice only) – to estimate the effect of providing lifestyle advice compared with no intervention; 2) Group 3 (phenotypic risk score and lifestyle advice) vs. Group 4 (phenotypic and genetic risk scores and lifestyle advice) – to estimate the effect of providing a genetic risk score in addition to lifestyle advice and a phenotypic risk score; 3) Group 3 + Group 4 vs. Group 1 – to estimate the effect of providing risk score information and lifestyle advice compared with no intervention, and 4) Group 3 + Group 4 vs. Group 2 – to estimate the effect of providing risk score information in addition to lifestyle advice.

Mean changes in objectively measured physical activity between baseline and 3-month follow-up will be analysed using analysis of covariance (ANCOVA). The ANCOVA model will model change (follow-up minus baseline) in objectively measured physical activity, adjusted for baseline. A test involving three degrees of freedom (3 d.f.) will be performed of the null hypothesis that there is no difference between the four randomised groups. If the p-value from this test is <0.01, this will imply that there are differences between the groups. The ANCOVA model will also be used to derive estimates of the differences in mean change and 95 % confidence intervals for each of the four pairwise comparisons described above. To avoid detracting the focus of the results from the overall 3 d.f. test, *p*-values for each of the pairwise comparisons will not be calculated.

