#### Multiplicity

Given the number of endpoints, randomised groups and therefore comparisons, the results for the primary endpoint will be regarded as convincing if the *p*-value from the 3 d.f. test is <0.01, while the results for each secondary endpoint will be regarded as convincing if the relevant *p*-value from the 3 d.f. test is <0.001.

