## Discussion

The INFORM randomised trial has been designed to contribute toward the understanding of the impact of provision of phenotypic and genetic CHD risk information on health-related behaviour change and other important clinical outcomes. Comparison between randomised trial arms will enable estimation of: 1) the effect of providing web-based lifestyle advice; 2) the effect of providing a genetic risk score in addition to lifestyle advice and a phenotypic risk score; 3) the effect of providing risk score information and lifestyle advice and 4) the effect of providing risk score information in addition to lifestyle advice. The INFORM study will also provide information on potential moderators and mediators between the intervention and health-related behaviour change and other clinical outcomes.

Even though the routine use of CVD risk scores is strongly advocated by most cardiovascular guidelines [10, 11], relatively little is reliably known about the benefits of the provision of different forms of CVD risk scores to individuals and about any potential harms (such as the possibility of increased anxiety or false reassurance). Previous systematic reviews [18, 19] have concluded that no robust recommendations can be made about the value of providing CVD risk information owing to limitations in previous studies, including lack of adequate power and lack of objective measures of health-related behaviours.

The INFORM study is well-placed to advance current knowledge on this topic because it is a trial that combines several advantages, including: a) power to identify clinically important differences between groups in this study’s principal outcomes; b) objective measures of health-related behaviours; c) simplicity of the interventions and relevance to primary care. If the intervention(s) in this trial prove to be effective, then the components of the intervention should be relatively easy to implement in primary care practice. Hence, the INFORM trial should provide a reliable evaluation of the impact of the provision of CVD risk information, thereby potentially informing policy decisions and guiding clinical practice about the routine use of CVD risk scores in primary care.

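### The stated 80% power and 1.25% level belong to a pairwise test; the trial is decided by a 3 d.f. test at p<0.01 whose power is not given

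*Protocol article*

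**What the plan says.** In the protocol article, under the sample size calculation for the randomised trial, the level is tied to pairwise testing: "To allow for four pairwise comparisons in the primary analysis, the significance level was set to" 1.25%. The paragraph then gives the result: "We calculated that 186 participants per group will be needed to detect this effect with 80 % power and 95 % confidence". With 20% attrition this becomes 233 per group, 932 in total.

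The section on analysis design defines the primary null hypothesis as no difference among the four groups. Of the test it says: "A test involving three degrees of freedom (3 d.f.) will be performed of the null hypothesis that there is no difference" between the groups, with p<0.01 taken as evidence that they differ. Four contrasts (1 v 2, 3 v 4, 3+4 v 1, 3+4 v 2) are estimated with 95% confidence intervals, but p-"values for each of the pairwise comparisons will not be calculated", so that attention stays on the overall test. The Multiplicity section repeats the rule: "the results for the primary endpoint will be regarded as convincing if the" 3 d.f. p-value is below 0.01.

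The Discussion lists among the trial's advantages "power to identify clinically important differences between groups in this study’s principal outcomes".

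**The concern.** The power statement and the decision rule refer to different tests. The first concerns a two-group comparison at 1.25%; the second is a four-group test at 1%. The article gives no power for the second, and the first is never carried out. The pairwise intervals are at 95%, not the 98.75% that would correspond to 1.25%.

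The power of a 3 d.f. test depends on the positions of all four group means, not only on one difference, so the 80% cannot simply be carried over. If the primary test is not significant, readers will judge that result against the stated 80% and the power claim in the Discussion. For some arrangements of the groups that would be too generous; for others it would be too cautious.

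**Working it through.** **Inputs from the sample-size paragraph:** 186 analysed per group, 80% power, 1.25% level, 20% attrition, equal allocation. **From the analysis and multiplicity sections:** 3 d.f. test, threshold 0.01. **Assumption:** the 1.25% is two-sided, which the article does not say.

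**Step 1: the plan's own figures.** 186/0.8 = 232.5, rounded up to 233; 4 × 233 = 932. Both reproduce. The 186 cannot be rebuilt forwards, because the article gives the effect as 10% without an absolute value, so it is inverted.

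**Step 2: implied detectable difference.** d = √(2/186) × (z₀.₉₉₃₇₅ + z₀.₈₀) = √(2/186) × (2.498 + 0.842) = 0.346 residual SD. Putting 0.346 back into the two-sample formula at 1.25% and 80% returns 186. Because d is in residual SD units, the SD of 0.05 and the correlation of 0.6 are not needed from here on.

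**Step 3: power of the deciding test.** The non-centrality is 186 × d² × k = 22.30 × k, where k is the sum of squared deviations of the four group means from their average, in units of d. The denominator degrees of freedom are 4 × 186 − 5 = 739 (four group means and one baseline covariate). Power comes from the non-central F distribution with 3 and 739 d.f. at level 0.01.

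| Means of Groups 1, 2, 3, 4 (units of d) | k | Non-centrality | Power |
|---|---|---|---|
| 0, 0, 1, 1 (two against two) | 1.000 | 22.30 | 94% |
| 0, 0, 0, 1 or 0, 1, 1, 1 (one against three) | 0.750 | 16.73 | 84% |
| 0, 2/3, 1, 1 (least favourable for 3+4 v 1) | 0.667 | 14.87 | 77% |
| 0, 1/3, 2/3, 1 (even gradient, d only between 1 and 4) | 0.556 | 12.39 | 67% |
| 1/2, 1/2, 0, 1 (Groups 1 and 2 midway between 3 and 4) | 0.500 | 11.15 | 60% |

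For a fixed largest difference between any two of four equal groups, 60% and 94% are the lower and upper bounds.

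**Step 4: restrict to the planned contrasts.** Suppose effects never reverse from Group 1 to Group 4, and one planned contrast equals d. The lowest 3 d.f. power is then 84% for 1 v 2 (means 0, 1, 1, 1), 84% for 3 v 4 (0, 0, 0, 1), 94% for 3+4 v 2 (0, 0, 1, 1) and 77% for 3+4 v 1 (0, 2/3, 1, 1).

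**Step 5: sensitivity to the level behind the 186.** If the 1.25% was one-sided, d = 0.320 and the bounds become 51% and 89%. If 5% two-sided was used, d = 0.291 and they become 40% and 80%. The mismatch between sizing and analysis is present under each reading.

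**The case against.** A reader might infer that the trial is underpowered for its primary test, with 60% as the headline. The documents do not support that. When one group differs by the target amount, the 3 d.f. test has 84% power, more than the stated 80%. The 67% gradient places d between Groups 1 and 4, which is not one of the four planned contrasts; 1 v 2 and 3 v 4 are then each d/3, where a pairwise test at 1.25% would have only about 8% power. If the gradient is scaled so that 3+4 v 1 equals d (means 0, 0.4, 0.8, 1.2; k = 0.8), the 3 d.f. power is 87%. The 60% case requires the phenotypic and genetic scores to act in opposite directions relative to advice alone. The Background's mention of a defeatist response makes such a reversal conceivable, but it is the mathematical worst case. All of this stands, and it limits the size of the finding.

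Other strong readings also fail:
- **Contradictory levels.** The 95% confidence may be the family-wise level, since 5%/4 = 1.25%. The phrase is unclear rather than shown to be wrong, and the 40% to 80% range in Step 5 is a sensitivity check only.
- **Incompatible SD and correlation.** An ANCOVA of change adjusted for baseline can use both: assuming equal variances, the residual SD is 0.05/√(2 × 0.4) × 0.8 = 0.0447. Nothing shows that another value was used.
- **Missing baseline mean.** A condensed article may leave this to the full protocol.

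It is also fair that the primary test and its threshold are stated clearly and consistently, and that 95% intervals will let readers judge the precision of a null result. None of this removes the mismatch: the article states a power and a level for a test that it then rules out.

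**Conclusion.** The concern holds in a limited form. The 80% power and 1.25% level describe a pairwise comparison, while the trial is decided by a 3 d.f. test at 0.01 for which no power is stated. At the difference implied by the plan's own 186 per group, that test has 84% to 94% power for the simplest patterns, 77% in the least favourable case for Groups 3+4 v 1, 67% for an even gradient across the extremes, and 60% at worst. Power therefore falls below 80% for some patterns and exceeds it for others.

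These figures rest on a two-sided 1.25% level and on inverting the 186, because the absolute effect is not given. The mismatch itself follows directly from the text and depends on neither.

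**What to change.** Rewrite the sample-size paragraph for the test that decides the trial:
- State the power of the 3 d.f. test at 0.01 with 186 analysed per group under named group patterns, such as those in the table.
- Either replace the 1.25% level and the 95% confidence with the level of the primary test, or keep them labelled as the pairwise basis for sizing and, if that is what was meant, the family-wise level.
- Qualify the power claim in the Discussion so that it refers to the patterns for which it holds.

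The four contrasts need not become the primary tests; that would reverse a choice which the analysis section makes deliberately and explains. The cost is wording, plus a stated power that is less favourable for some patterns. No additional participants are needed.

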#### Sample size – qualitative study

A sample size of between 30 and 35 male and female participants will be selected purposively, mainly from the intervention arms to include people with various demographic backgrounds. This sample size is common for this kind of study [57, 58] and is consistent with the time resources required for this type of data analysis and the predicted range of number of interviews required for achieving saturation.

#### Analysis design – randomised controlled trial

All trial analyses will be based on the Intention To Treat (ITT) principle. Those with missing follow-up data will be excluded from the analyses (a complete case approach). We will perform sensitivity analyses to assess the impact of missing follow-up data on the results. Participants with missing baseline data will be included in the analyses using the missing-indicator method [59].

The null hypothesis for the primary analysis is that there is no difference between any of Groups 1 to 4. Estimates of the following pairwise differences will be calculated: 1) Group 1 (control group) vs. Group 2 (lifestyle advice only) – to estimate the effect of providing lifestyle advice compared with no intervention; 2) Group 3 (phenotypic risk score and lifestyle advice) vs. Group 4 (phenotypic and genetic risk scores and lifestyle advice) – to estimate the effect of providing a genetic risk score in addition to lifestyle advice and a phenotypic risk score; 3) Group 3 + Group 4 vs. Group 1 – to estimate the effect of providing risk score information and lifestyle advice compared with no intervention, and 4) Group 3 + Group 4 vs. Group 2 – to estimate the effect of providing risk score information in addition to lifestyle advice.

Mean changes in objectively measured physical activity between baseline and 3-month follow-up will be analysed using analysis of covariance (ANCOVA). The ANCOVA model will model change (follow-up minus baseline) in objectively measured physical activity, adjusted for baseline. A test involving three degrees of freedom (3 d.f.) will be performed of the null hypothesis that there is no difference between the four randomised groups. If the p-value from this test is <0.01, this will imply that there are differences between the groups. The ANCOVA model will also be used to derive estimates of the differences in mean change and 95 % confidence intervals for each of the four pairwise comparisons described above. To avoid detracting the focus of the results from the overall 3 d.f. test, *p*-values for each of the pairwise comparisons will not be calculated.

For each continuous secondary endpoint, the four pairwise differences will be estimated, together with 95 % confidence intervals, using ANCOVA as described for the primary outcome analyses (except Coronary Heart Disease-related Worry). The Coronary Heart Disease-related Worry will be measured only at follow-up, so the four pairwise differences will be estimated, together with 95 % confidence intervals, using linear regression. A 3 d.f. test will be performed of the null hypothesis that there is no difference between the four randomised groups. For categorical endpoints, similar analyses will be performed using logistic and multinomial regression models.

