### Randomisation, allocation concealment and blinding

Randomisation of the INFORM participants is undertaken centrally at the trial coordinating centre at the Department of Public Health and Primary Care, University of Cambridge. The study involves individual-level randomisation using a computer program built into the study database. This programme is designed and implemented by the data manager. Randomisation is stratified by age (≤ or > 60 years) and sex in order to balance baseline phenotypic risk across study groups. Given the nature of the trial, it is not possible to blind participants to which intervention they receive. However, an independent data manager (not involved in designing the study) oversees the randomisation and data collection process. Additionally, the researchers assessing the trial outcomes will remain blinded to the allocation of interventions. As the participants for the qualitative part of the study are purposively selected, the qualitative researchers have access to the information collected during baseline assessment and treat it as confidential.

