#### Subgroup analyses

For the primary endpoint, the ANCOVA model will be extended to include an interaction between the intervention effect and (1) age (continuous variable), (2) baseline phenotypic CHD risk score (continuous variable) and (3) sex. If the p-value for interaction is <0.05, then the number and percentage of individuals with the endpoint within each randomised group, together with intervention effect (and 95 % confidence intervals) will be reported separately within categories defined by the subgroup variable. For age and baseline CHD risk score, the cut-off for the categories will be their median values at baseline.

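### Randomisation is stratified by age and sex but the stated ANCOVA adjusts only for baseline activity; if these factors predict change, intervals are slightly too wide and some precision is forgone

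*Protocol article*

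**What the plan says.** All references are to the protocol article.

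- **Randomisation, allocation concealment and blinding:** "Randomisation is stratified by age (≤ or > 60 years) and sex in order to balance baseline phenotypic risk across study groups". The reason given is balance of CHD risk, not prognosis for physical activity.
- **Analysis design – randomised controlled trial, primary outcome:** "The ANCOVA model will model change (follow-up minus baseline) in objectively measured physical activity, adjusted for baseline". Baseline activity is the only covariate named. The decision rule follows: "If the p-value from this test is <0.01, this will imply that there are differences between the groups". The same model supplies "95 % confidence intervals for each of the four pairwise comparisons described above", and no pairwise p-values are to be calculated.
- **Same section, secondary endpoints:** continuous endpoints are analysed "using ANCOVA as described for the primary outcome analyses". CHD-related worry, treated there as measured only at follow-up, has a linear regression with no covariate named. Categorical endpoints have similar analyses by logistic and multinomial regression.
- **Subgroup analyses:** age and sex come in only here, where "the ANCOVA model will be extended to include an interaction between the intervention effect and (1) age (continuous variable") and likewise with baseline CHD risk score and with sex. Describing this as an extension supports reading the main model as not containing them.

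**The concern.** Stratified allocation balances the arms on age and sex by design. The true variance of a treatment contrast then no longer contains a contribution from chance imbalance in those factors. A model that leaves them out still counts their variation as residual noise. The reported standard error is therefore larger than the actual variability of the estimate, provided that the factors carry information about the outcome beyond baseline activity.

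Precision and calibration are at stake, not validity. The 3 d.f. test would reject a true null less often than the stated 0.01, the intervals for the four contrasts would cover slightly more than 95 %, and a little power would be left unused. The article does not merely stay silent on covariates. It names an adjustment set, and that set omits the design factors.

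**Working it through.** **Inputs from the document.** Sample size section: 186 evaluable per group, 80 % power, significance level 1.25 % (taken as two-sided, which is not stated), 20 % attrition, 932 randomised. Analysis section: 3 d.f. test at 0.01.

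**Input not in the document.** R², the share of residual variance that age and sex explain once baseline activity is in the model. I take 0, 2, 5 and 10 % as an assumed range.

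**Step 1: the plan's own figures.** 186 / (1 − 0.20) = 232.5, rounded up to 233, and 4 × 233 = 932. This reproduces. The 186 itself cannot be rebuilt, because the effect is given as 10 % with no baseline mean. It can be turned into a standardised difference: z for 1.25 % two-sided is 2.498, z for 80 % power is 0.842, and (2.498 + 0.842) / √(186/2) = 3.339 / 9.644 = 0.346 residual SDs. The plan's 80 % does not draw on stratum adjustment.

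**Step 2: interval width.** Adjustment multiplies the residual SD, and so the standard error, by √(1 − R²). The unadjusted interval is wider by the factor 1/√(1 − R²).

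**Step 3: pairwise power at the sample-size settings.**
- Adjusted: Φ(3.339/√(1 − R²) − 2.498).
- Unadjusted: Φ(0.842/√(1 − R²)), because the test uses the inflated standard error while the estimate varies less than that.

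**Step 4: true size of the 3 d.f. test at 0.01 without adjustment.** Large-sample approximation: P(χ²₃ > 11.345/(1 − R²)).

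| R² (assumed) | Unadjusted interval wider by | Power unadjusted | Power adjusted | Power forgone (points) | True size of 0.01 test, unadjusted |
|---|---|---|---|---|---|
| 0 % | 0 % | 80.0 % | 80.0 % | 0 | 0.0100 |
| 2 % | 1.0 % | 80.2 % | 80.9 % | 0.7 | 0.0090 |
| 5 % | 2.6 % | 80.6 % | 82.3 % | 1.7 | 0.0076 |
| 10 % | 5.4 % | 81.3 % | 84.7 % | 3.4 | 0.0056 |

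Steps 3 and 4 assume full balance within strata among those analysed.

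**Step 5: simulation check.** Four arms of 186 balanced within the four strata, ANCOVA with and without the strata, F test at 0.01. There were 4,000 runs under the null and 2,000 with all three active arms 0.345 residual SDs above control.

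| R² | Adjusted interval narrower by | Type I error, omitted / included | Coverage under the null, omitted / included | Power of 3 d.f. test, omitted / included |
|---|---|---|---|---|
| 0 % | 0 % | 0.010 / 0.010 | 94.9 / 94.8 % | 82.5 / 82.4 % |
| 2 % | 1.0 % | 0.009 / 0.010 | 95.2 / 95.0 % | 84.2 / 85.4 % |
| 5 % | 2.6 % | 0.009 / 0.012 | 95.8 / 95.4 % | 82.4 / 85.3 % |
| 10 % | 5.2 % | 0.0065 / 0.0105 | 96.1 / 95.1 % | 84.0 / 87.9 % |

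With 4,000 runs the Monte Carlo standard error of a rate of 0.01 is √(0.01 × 0.99 / 4000) = 0.0016, so only the 10 % row separates clearly from 0.01. Direction and order of magnitude agree with the formulas. The power forgone is about 0 to 4 points.

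**The case against.** The strongest reply is that no harm is shown. The loss exists only if age and sex predict 12-week change after baseline activity is in the model. The document gives no such figure and justifies the strata by CHD risk. At R² = 0 the simulated intervals and type I error are the same either way. This stands, and it makes the point conditional.

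A reader might infer that the omission leaves the trial underpowered. The document does not support that. The 80 % was planned without stratum adjustment, and unadjusted power does not fall below it at any R² in the table. What is given up is a possible gain. Nor can a firm power figure be put on the 3 d.f. test, since that needs a pattern of four means that the article does not give. The simulated values rest on one assumed pattern.

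The conservatism shown is also an upper bound. The article does not say how balance within strata is achieved, and a complete-case analysis with an expected 20 % attrition lets some chance imbalance back in.

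The residual-variance argument does not carry over to logistic and multinomial models. There, adding covariates moves the target to a conditional odds ratio and need not tighten the interval. That objection stands in full.

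Finally, the article condenses a fuller protocol and mentions a predefined analysis plan, either of which may list more covariates. That is possible, but the text at hand states the adjustment set rather than leaving it open.

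In the other direction, participants whose baseline monitor is never returned are still randomised and are kept by the missing-indicator method. For them baseline activity explains nothing, so age and sex may carry more information. The worry regression has no baseline term at all.

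**Conclusion.** The mismatch between design and stated model is real, and its consequence is small and one-sided. If age and sex explain 2 to 10 % of residual variance after baseline activity, the 95 % intervals are about 1 to 5 % wider than needed, the 3 d.f. test runs somewhat below its nominal 0.01, and up to about 4 points of power are forgone. If they explain nothing, nothing is lost. Estimates are not biased and false positives are not inflated, so no conclusion reached under the stated model would be invalid for this reason. The sizes rest on the assumed range for R², on a two-sided test, and on near-complete balance within strata among those analysed. The point applies to the linear models only. It is a low-priority improvement, worth making because it costs almost nothing and because the stated thresholds (0.01 primary, 0.001 secondary) are already strict.

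**What to change.** State in the analysis section that the primary ANCOVA includes baseline activity, sex and age, with age either continuous (as the subgroup section already uses it) or as the 60-year stratum. Apply the same covariates to the linear models for the continuous secondary endpoints, including the linear regression for CHD-related worry. If the investigators prefer to leave the factors out, say so and give the reason.

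For the logistic and multinomial models, adjustment is optional. If it is adopted, the ground is consistency with the design, and the report should say that the odds ratios are then conditional on age and sex.

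The cost is a sentence of wording and two degrees of freedom (sex and age), or three if all four strata are fitted, out of about 744 evaluable participants (4 × 186). Both variables are used to randomise, so they are known for everyone. Settling this before the data are analysed also avoids a later choice of covariates.
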